# Effectiveness of topical silicone gel and pressure garment therapy for burn scar prevention and management in children: study protocol for a randomised controlled trial

**DOI:** 10.1186/s13063-017-1820-z

**Published:** 2017-02-16

**Keywords:** Burns, Scar management, Randomised controlled trial, Topical silicone gel, Pressure garment therapy, Children

## Abstract

**Background:**

Abnormal scar development following burn injury can cause substantial physical and psychological distress to children and their families. Common burn scar prevention and management techniques include silicone therapy, pressure garment therapy, or a combination of both.

Currently, no definitive, high-quality evidence is available for the effectiveness of topical silicone gel or pressure garment therapy for the prevention and management of burn scars in the paediatric population. Thus, this study aims to determine the effectiveness of these treatments in children.

**Methods:**

A randomised controlled trial will be conducted at a large tertiary metropolitan children’s hospital in Australia. Participants will be randomised to one of three groups: Strataderm® topical silicone gel only, pressure garment therapy only, or combined Strataderm® topical silicone gel and pressure garment therapy. Participants will include 135 children (45 per group) up to 16 years of age who are referred for scar management for a new burn. Children up to 18 years of age will also be recruited following surgery for burn scar reconstruction. Primary outcomes are scar itch intensity and scar thickness. Secondary outcomes include scar characteristics (e.g. colour, pigmentation, pliability, pain), the patient’s, caregiver’s and therapist’s overall opinion of the scar, health service costs, adherence, health-related quality of life, treatment satisfaction and adverse effects. Measures will be completed on up to two sites per person at baseline and 1 week post scar management commencement, 3 months and 6 months post burn, or post burn scar reconstruction. Data will be analysed using descriptive statistics and univariate and multivariate regression analyses.

**Discussion:**

Results of this study will determine the effectiveness of three noninvasive scar interventions in children at risk of, and with, scarring post burn or post reconstruction.

**Trial registration:**

Australian New Zealand Clinical Trials Registry, ACTRN12616001100482. Registered on 5 August 2016.

**Electronic supplementary material:**

The online version of this article (doi:10.1186/s13063-017-1820-z) contains supplementary material, which is available to authorized users.

## Introduction

The protocol for this study has been reported as per the Standard Protocol Items: Recommendations for Interventional Trial (SPIRIT) guidelines (Additional File 1) [1].

## Background

With post-burn mortality rates declining, the greatest burden to burn centres is scarring [2–4]. In children, scarring has substantial ramifications for the child’s physical and psychological functioning as well as health-related costs for the family and the health care service [5]. Factors associated with risk of scarring in children include total body surface area (TBSA) burned, delayed wound healing, deep burn injuries, skin type, anatomical burn site and skin grafting [2, 6–9].

Abnormal scars have a documented prevalence rate of 32 to 72% post burn [6, 10] and are defined as scars with physical and sensory symptoms that impact on health-related quality of life due to itch, raising, pain, tightness and contracture formation [5, 10]. Qualitative research has also shown that the appearance and the impact of scars must be considered from the patient’s perspective, not just the perspective of the treating clinical team [11, 12]. Scar prevention and management interventions are initiated with the goal of preventing or reducing scar itch, thickness, erythema and pliability with the ultimate goal of maintaining or improving overall appearance of the scar and quality of life [13–18].

Scar thickness has traditionally been one of several characteristics used to define the severity of scarring and is included in most scar rating scales. A meta-analysis of studies of pressure garment therapy effectiveness, a recent systematic review of noninvasive scar interventions, including silicone products and pressure garments and a longitudinal study of scarring in people with burns receiving standard scar management, have supported the importance of measuring scar thickness [2, 17, 19]. Scar thickness has been found to be the characteristic that most clearly distinguishes normal scar and normal skin from hypertrophic scars up to 12 months post burn [19].

Itch has been found post discharge in approximately 80% of patients after burn injury and has been reported to persist for a prolonged period post burn [20, 21]. This symptom has a sustained debilitating impact on patients, influencing wound healing, psychological wellbeing, and engagement in activities of daily living [20, 21]. It is, therefore, important that the prevention and management of burn scars is optimum to reduce the impact of scar sequelae, such as itch, on psychosocial development and health-related quality of life including the child’s ability to independently complete daily activities; and to prevent future invasive scar interventions.

Burn scar prevention and management after skin healing in high-income countries currently includes the use of silicone products or pressure garment therapy or pressure garment therapy combined with silicone products [5]. These treatments have been routine practice for burn scar prevention and management in high-income countries for over 40 years though their effectiveness remains unclear, particularly in children [5, 10, 13].

Silicone products can include topical silicone gels, silicone gel sheets, silicone sprays and silicone oils [22]. A film-forming topical silicone gel was selected for inclusion in this study as topical silicone gels have been recently recommended over other silicone products in clinical practice guidelines as they are thought to result in fewer adverse effects [23]. Strataderm® topical silicone gel, a product used in the participating burns department prior to the trial commencing, has the advantage of a reduced frequency of application (once per day as opposed to twice per day) compared to other topical silicone gel products. It, therefore, has the potential to reduce the treatment burden to patients, improve adherence and reduce the cost of scar prevention and management compared to other scar therapies. Whilst the exact mechanism of action of topical silicone gels has not been confirmed [22–24], it is hypothesised that the occlusive nature of the gel reduces transepidermal water loss, thus increasing the hydration of the stratum corneum [25, 26]. This results in a ‘normalising’ of the cellular processes of the skin, consequently reducing collagen production [25, 26]. Topical silicone gel may also provide a protective barrier against environmental contaminants [25, 26]. It is important to note, however, that whilst there is a reduced risk of adverse effects with the use of topical silicone gels there is still a risk of local dermatological reactions [25].

Pressure garment therapy also works to normalise cellular processes; however, it does this through mechanical pressure. Pressures of 15 to 25 mmHg are hypothesised to reduce capillary flow [13, 18], thus limiting oxygen and nutrients in the affected area and preventing collagen production [27]. The burden of pressure garment therapy to patients and their families, however, can be high if recommended wearing times of 23 h per day for up to 18 months or until scar maturation are followed [2, 28]. Adverse effects from pressure garment therapy can include skin breakdown, altered bone growth and psychological distress from cosmetic differences [2, 5, 7, 29]. The burden of treatment and the presence of adverse effects can impact patient adherence to recommended prevention strategies and requires careful consideration when evaluating the effectiveness of these interventions.

Previous studies have focused solely on the effectiveness of scar management interventions in relation to physical scar characteristics such as itch, height, pain, erythema, and range of motion [17]. They have not considered the broader evaluation of treatment burden (including adverse events), health-related quality of life, or cost-effectiveness [30]. Also, past studies evaluating the effectiveness of topical silicone gels and pressure garments have either not included children, or where children have been included, the numbers have been small or have been case study reports [16, 24, 31]. To overcome the limitations of the evidence in paediatrics, adequately powered, randomised controlled studies that use a broad evaluation framework are required. Thus, a randomised controlled trial (RCT) of the effectiveness of topical silicone gel and pressure garment therapy in children will be conducted using such a framework.

### Objectives

This study aims to determine the effectiveness of topical silicone gel versus pressure garment therapy versus combined topical silicone gel and pressure garment therapy, in the prevention and management of burn scars in children aged 0 to16 years post burn or 0 to18 years post burn scar reconstruction. This will be investigated using the primary outcomes of scar itch and thickness at 6 months post burn or burn scar reconstruction. Current medical literature has been unable to demonstrate one treatment group as being superior to the others; however, we hypothesise that there will be at least one pairwise difference between the group means for scar thickness at the 6-month endpoint.

## Methods

### Study design

A randomised controlled trial with three parallel arms will be conducted to examine the effectiveness of Strataderm® topical silicone gel, pressure garment therapy, and combined topical silicone gel and pressure garment therapy for the prevention and management of burn scars in children. Individual randomisation by patient will be undertaken using computer-generated random numbers. Randomisation will occur using a 1:1:1 ratio between groups in blocks of 12 and will be stratified by surgical intervention received (i.e. skin grafting in the acute phase, spontaneous skin healing in the acute phase, post-acute reconstructive surgery). Concealment of treatment allocation will be completed by the use of sealed, opaque, identical and serially numbered envelopes prepared in advance by an independent party. All outcomes will be measured at baseline (scar intervention commencement), 3 months and 6 months post burn or reconstruction. The primary outcome measures and the level of pressure beneath pressure garments will also be measured at 1 week post baseline. This project has ethics approval from the Child Health Queensland Human Research Ethics Committee (HREC). A flow diagram of the data collection process is displayed in Fig. 1.

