### Intervention

Participants will receive standard care for the acute burn injury as determined by the burns multidisciplinary team. If a participant is recommended for scar management and their caregiver provides consent to participate, baseline assessment will be completed. Participants will then be randomly allocated into one of three scar management intervention groups according to the contents of the sealed envelope opened by an independent party. Group 1 will receive medical use topical silicone gel (Strataderm®). Group 2 will receive pressure garment therapy (Therapeutic Support Laboratory) only. Group 3 will receive a combination of topical silicone gel (Strataderm®) and pressure garment therapy. The intervention products will be provided to the patient as per standard practice once the skin is healed (e.g. sufficient topical silicone gel will be provided to allow coverage of the scar area until the next appointment and two sets of pressure garments will be provided to each child participant at a new fitting).

The study follow-up time periods will match standard occupational therapy review times (e.g. 3 months and 6 months post burn).

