### Blinding

Baseline measures will be completed prior to randomisation. Due to the nature of the study double blinding will not be possible as treating therapists and patients and their families will be aware of the treatment modality. Investigator blinding will be difficult to maintain within this environment; therefore, the primary investigator will complete all outcomes measures without blinding. Ultrasound images and the measurement of burn scar thickness using the images taken by the primary investigator will be completed in real time at baseline, 1 week and 3- and 6-month follow-up points. However, at the conclusion of data collection a second investigator (blinded to the results during data collection and to the patient’s identity – nonidentifiable to the second investigator) will measure burn scar thickness using the ultrasound images taken by the primary investigator. Only the results of the blinded assessor will be used in data analysis. The inter-rater variation between the investigators will be reported for the study.

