## Trial status

Recruitment commenced at the end of August 2016 and it is expected that recruitment will take approximately 1 year to complete with final data collection occurring in February 2018.

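### A single fixed block size of 12, printed during recruitment into an open single-hospital trial, lets anyone who tallies by stratum infer the last allocation of each completed block

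*Protocol article*

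**What the plan says.** Study design fixes the scheme: "Randomisation will occur using a 1:1:1 ratio between groups in blocks of 12 and will be stratified by surgical intervention received". The three strata are "skin grafting in the acute phase, spontaneous skin healing in the acute phase, post-acute reconstructive surgery". The same section describes the concealment: "Concealment of treatment allocation will be completed by the use of sealed, opaque, identical and serially numbered envelopes prepared in advance by an independent party". Intervention adds that allocation is made "according to the contents of the sealed envelope opened by an independent party".

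On the order of events, Intervention says that once a child is recommended for scar management and "their caregiver provides consent to participate, baseline assessment will be completed", with allocation following. Blinding confirms it: "Baseline measures will be completed prior to randomisation". Blinding also says that therapists and families will know the treatment and that "the primary investigator will complete all outcomes measures without blinding". For scar thickness, a second investigator later re-measures the stored images blinded, and only those readings are analysed.

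The Abstract places the trial at one hospital. The article is dated 16 February 2017. Trial status says "Recruitment commenced at the end of August 2016" and expects about one year of recruitment, so the block size was printed inside the planned recruitment window. The article does not say that the block size varies, that it is withheld from trial staff, or who approaches and enrols children.

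**The concern.** Sealed envelopes hide the next card. They do not hide what can be deduced from the cards already opened. With one known block size, an observer who has seen the earlier allocations in a stratum knows how many cards of each arm remain. When only one arm is left, the next allocation is known before the envelope is touched. The stratum is also known by then, because it is the surgical history.

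At one open hospital, such a tally of three arms in three strata is easy to keep. Consent and baseline assessment, and with them the choice of up to two scar sites, come before allocation. That order normally protects a trial, but it does not when the next arm can be inferred. Three things could be influenced:

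- when, or whether, a child is approached; one exclusion criterion turns on whether a comorbidity might affect the primary outcomes, which needs judgement;
- which scar site is studied;
- how the baseline ultrasound image is taken; baseline values are adjusted for in the primary model.

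The Discussion expects better adherence with gel than with garments, so staff may hold expectations about which child suits which arm.

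**Working it through.** **Inputs.** From the article: three arms at 1:1:1, blocks of 12 (so 4+4+4), three strata, 135 participants. Stratum sizes are not given, so the splits below are assumptions. The observer is assumed to know the block size and every earlier allocation in the stratum.

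**The plan's own figure.** The total of 135 reproduces: 36 / (1 − 0.20) = 45 per group, and 3 × 45 = 135. The point uses it only as a denominator.

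**Allocations known with certainty.** An allocation is certain when all remaining cards belong to one arm.

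- 12th: 1
- 11th (last two cards alike): 3/11 = 0.273
- 10th (last three alike): (3/11)(2/10) = 0.055
- 9th (last four alike): (3/11)(2/10)(1/9) = 0.006
- 1st to 8th: never

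Sum: 1.33 per block, or 1.33/12 = 11.1%.

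**Allocations with at least one arm ruled out.** With r cards left, the probability that at least one arm is absent is [3·C(8,r) − 3·C(4,r)] / C(12,r).

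| Position | r | Probability |
|---|---|---|
| 12 | 1 | 1 |
| 11 | 2 | (84 − 18)/66 = 1 |
| 10 | 3 | (168 − 12)/220 = 0.709 |
| 9 | 4 | (210 − 3)/495 = 0.418 |
| 8 | 5 | 168/792 = 0.212 |
| 7 | 6 | 84/924 = 0.091 |
| 6 | 7 | 24/792 = 0.030 |
| 5 | 8 | 3/495 = 0.006 |

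Sum: 3.47 per block, or 28.9%. This count includes the certain ones.

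**Best guess.** Always naming the arm with most cards left is right for 6.14 of 12 allocations (51.2%), against 33.3% by chance.

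**Whole trial, allowing for incomplete blocks.**

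- 45/45/45: each stratum holds three full blocks plus 9. Certain: 3 × (3 × 1.333 + 0.006) = 12.0. At least one arm ruled out: 3 × (3 × 3.467 + 0.758) = 33.5, where 0.758 is the sum over positions 5 to 9.
- 40/90/5: 3, 7 and 0 full blocks, with remainders of 4, 6 and 5. Certain: 10 × 1.333 = 13.3. At least one arm ruled out: 10 × 3.467 + 0.036 + 0.006 = 34.7.
- Sensitivity: 60/60/15 gives 14.7 and 38.1. The bound if every block were complete is 11.25 × 1.333 = 15 and 11.25 × 3.467 = 39. It cannot be reached, because 135 is not a multiple of 12.

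**Varying block sizes.** Simulation with sizes drawn with equal probability; the observer knows the set of sizes but not their order. Ranges cover the 45/45/45 and 40/90/5 splits.

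| Scheme | Certain, of 135 | At least one arm ruled out, of 135 | Best guess right |
|---|---|---|---|
| Fixed 12 | 12–13 | 33–35 | about 50% |
| 9, 12, 15 | about 2 | about 7 | about 50% |
| 6, 9, 12 | about 3 | about 9 | about 52% |
| 3, 6 | about 11 | about 29 | about 57% |

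Larger varying blocks remove most of the certain knowledge without changing average guessability. Small varying blocks leave nearly as much certain knowledge as now and raise guessability.

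**The case against.** The strongest reply is that a large fixed block with independently prepared and opened envelopes is a conventional choice, and that the exposure is limited. Much of this stands:

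- Twelve is large for three arms. A fixed block of 6 would make 20% of allocations certain, against 11% here, and the first eight in a block are never certain.
- Exploiting the scheme needs a correct tally in each stratum and knowledge of where blocks begin. The article does not say who enrols, so it is not established that the person best placed to keep the tally can also act on it.
- Itch is reported by the child or caregiver, who cannot know the running count.
- Thickness is analysed only from the blinded reader's values, baseline included. The image is to be taken centrally and three measurements averaged.
- Publication probably told the trial team nothing new.

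A reader might infer that concealment fails at the end of each block, or that the result will carry selection bias beyond repair. The documents support neither. They show an opportunity, not its use, and the planned adjustment covers the baseline outcome and those listed confounders, anatomical site among them, that turn out imbalanced.

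Two parts of the reply do not stand. An independent opener does not prevent inference from the count. A blinded reader cannot correct who was enrolled, which site was chosen or how the image was taken, and adjustment cannot reach unmeasured features such as expected tolerance of garments.

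**Conclusion.** The point holds as a modest, avoidable design weakness. For an observer with a correct tally by stratum, about 12 to 13 of 135 allocations would be certain in advance, and about 33 to 35 would have at least one arm ruled out, under splits of 45/45/45 or 40/90/5. Other splits can bring this close to 15 and 39. Where only one arm is ruled out, two remain possible, so those cases are partial information and not foreknowledge. The exposure concerns enrolment timing, site choice and image taking; no bias in the result has been shown or sized. The change is worth making because the trial is open, at one hospital, and the remedy is cheap.

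**What to change.** Have the independent party replace the unused envelopes in each stratum with a new computer-generated list in randomly varying block sizes that are not small, for example 9, 12 and 15. Withhold both the sizes and their order from everyone who recruits, takes consent or measures. Avoid sizes of 3 or 6, which raise guessability. State in the protocol only that randomly varying blocks are used, and give the sizes after recruitment closes.

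The expected gain is the fall in certain and partly revealed allocations shown above. It should be described as removing certain knowledge, since the best-guess rate stays near 50%. Those figures assume the scheme runs from the first participant; allocations already made under blocks of 12 keep their exposure.

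The cost is a new list and re-packed envelopes, with no extra participants or staff. The downside is slightly larger possible imbalance within a stratum when a block is left incomplete: the largest difference between two arms in an unfinished block is 4 with a block of 12 and 5 with a block of 15.

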**Fig. 1 Fig1:**
[figure not shown]
Flow diagram of data collection

A measure of fidelity will assist in determining whether the outcomes are a result of the intervention or the processes involved in delivering the intervention (e.g. the education of participants and caregivers by therapists) [32]. Checklists will be used to record whether the critical elements of the intervention have been delivered as a measure of fidelity. The fidelity checklist includes items regarding mechanism of action of allocated treatment, skin care, sun care, wear and care instructions of allocated treatment and potential adverse effects.

### Setting

The primary setting for data collection will be a burns unit at a large tertiary metropolitan children’s hospital in Australia. Children who access this unit are predominantly male (60%), under the age of 2 years and most frequently present with a scald or a contact burn injury. The incidence of flame and friction burns increases with age [33]. The primary setting provides outreach services via telehealth and receives patients from the Pacific Islands and interstate if required. If necessary, measurements may be taken at a colocated research centre, or the hospital in the patient’s local health district, and/or at the client’s home to reduce potential burden for participants (and their families) and minimise participant dropout.

